## Abstract

**Background:**

As an indigestible component of human breast milk, Human Milk Oligosaccharides (HMOs) play an important role as a substrate for the establishing microbiome of the newborn. They have further been shown to have beneficial effects on the immune system, lung and brain development. For preterm infants HMO composition of human breast milk may be of particular relevance since the establishment of a healthy microbiome is challenged by multiple disruptive factors associated with preterm birth, such as cesarean section, hospital environment and perinatal antibiotic exposure. In a previous study it has been proposed that maternal probiotic supplementation during late stages of pregnancy may change the HMO composition in human milk. However, there is currently no study on pregnancies which are threatened to preterm birth. Furthermore, HMO composition has not been investigated in association with clinically relevant outcomes of vulnerable infants including inflammation-mediated diseases such as sepsis, necrotizing enterocolitis (NEC) or chronic lung disease.

**Main body:**

A randomized controlled intervention study (PROMO = probiotics for human milk oligosaccharides) has been designed to analyze changes in HMO composition of human breast milk after supplementation of probiotics (*Lactobacillus acidophilus*,* Bifidobacterium lactis* and *Bifidobacterium infantis*) in pregnancies at risk for preterm birth. The primary endpoint is HMO composition of 3-fucosyllactose and 3’-sialyllactose in expressed breast milk. We estimate that probiotic intervention will increase these two HMO levels by 50% according to the standardized mean difference between treatment and control groups. As secondary outcomes we will measure preterm infants’ clinical outcomes (preterm birth, sepsis, weight gain growth, gastrointestinal complications) and effects on microbiome composition in the rectovaginal tract of mothers at delivery and in the gut of term and preterm infants by sequencing at high genomic resolution. Therefore, we will longitudinally collect bio samples in the first 4 weeks after birth as well as in follow-up investigations at 3 months, one year, and five years of age.

**Conclusions:**

We estimate that probiotic intervention will increase these two HMO levels by 50% according to the standardized mean difference between treatment and control groups. The PROMO study will gain insight into the microbiome-HMO interaction at the fetomaternal interface and its consequences for duration of pregnancy and outcome of infants.

## Background and literature research

Human Milk Oligosaccharides (HMOs) are the third largest component of human milk [2, 3]. Reported concentrations range from 5-15 g/l in mature milk up to 20 g/l in colostrum [2, 4]. More than 200 different HMOs have been identified although < 20 of them account for > 90% of total content [5]. HMO concentrations differ depending on maternal factors (age, parity, diet, ethnicity) [6], lactation period, length of gestation and mother’s genetic secretor status [4]. Glycosyltransferases synthesize five monosaccharides (ß-D-galactose(Gal), ß-D-glucose(Glc), ß-*N*-acetylglucosamine(Glc*N*Ac), α-L-Fucose(Fuc) and α-D-*N*-acetylneuraminic acid (Sia)) into the different HMOs [2, 5] in the Golgi apparatus of the mammary gland cells. The concentrations of HMOs in human milk vary greatly depending on the maternal expression of the secretor gene (FUT2) and the Lewis gene (FUT3) [7, 8]. Dominant (Se) and recessive (se) alleles are differentiated and mothers can be divided in ”secretors” and “non-secretors” with and without at least one dominant allele [9–11]. Hence, the total amount of HMOs in ”non-secretors” women’s milk is significantly lower compared to that of ”secretors” [12].

HMOs exert their prebiotic effect on the microbiome in the colon [13], where they are consumed by certain groups of the microbiota such as *Bifidobacteria*, strengthen their abundance, improve the mucosal barrier and unfold immunomodulatory effects [14, 15]. They may operate as antimicrobials and prevent adhesion of pathogens by entrapping specific receptors [5]. Potential positive effects on neurocognitive development have been described, however the exact mechanisms are yet unknown [14, 16]. While HMOs form the nutritional basis for specific strains of *Bifidobacteria* [13, 17–19], most pathogenic Enterobacteriaceae are unable to utilize HMOs [20]. By favoring *Bifidobacterium. infantis* in the gastrointestinal microbial community, HMOs support immunological maturation, limit excessive inflammation and intestinal permeability. In terms of clinical outcomes, the provision of breast milk with HMOs has been associated with a decreased risk for infections, improved growth and neurodevelopmental outcomes [21, 22]. Beneficial modulatory effects on the microbiome – immunity coevolution during the first months of life [15] may explain associated risk reductions for atopic diseases and asthma [23]. In preterm infants, HMOs may prevent gut dysbiosis [24, 25] and high concentrations of specific oligosaccharides (disialyllacto-*N*-tetraose) are associated with a lower risk for necrotizing enterocolitis (NEC) [26, 27]. However, research on clinical outcomes in this study population is very limited even though preterm infants are particularly vulnerable to microbiome disturbances, sustained inflammation [28] and associated adverse outcomes [29].

Recently, first approaches to optimize the composition of HMOs in human milk have been undertaken. In a study with infants at term, Seppo et al. [1] demonstrated changes in HMO composition in breast milk after supplementation of probiotics during pregnancy, e.g. increased levels of 3-fucosyllactose.

Here, we report on the methodology of a first randomized controlled intervention study with the PICO question, whether in the **P**opulation of pregnant women > 20 + 0 weeks of gestation at risk for preterm birth between 22 + 0 and 36 + 6 weeks of gestation the **I**ntervention of daily intake of *Lactobacillus acidophilus*,* Bifidobacterium animals* subsp. *lactis and Bifidobacterium. infantis* as compared to **C**ontrol (no probiotic intake) changes the **O**utcome HMO concentration and composition in human breast milk. Specifically, we hypothesize 50% increased amounts of 3-fucosyllactose and 3’-sialyllactose after supplementation [1]. Further hypotheses are that the supplementation of *Lactobacillus acidophilus* and *Bifidobacterium animalis* subsp. *lactis and Bifidobacterium. infantis* probiotics during pregnancy increases.

The number of several prebiotic HMOs (e.g. 3-fucosyllactose and 3’-sialyllactose) in breast milk.The abundance of *Lactobacillus* and *Bifidobacteria* in women’s vaginal flora.The abundance of *Lactobacillus* and *Bifidobacteria* in the neonatal microbiome of preterm infants.

Probiotics have been supplemented in several studies to pregnant women defining various hypotheses and outcomes. In preparation of our trial, we performed an extensive review of the scientific literature including (a) randomized placebo-controlled trials that have been (b) recently published (between 2010 and 2022), that (c) supplemented groups of *Bifidobacteria* spp. and/or *Lactobacillus* spp. to (d) pregnant women with an (e) minimum sample size of *n* = 30 women supplemented. We searched PubMed using the terms “probiotics” AND/OR “pregnancy” OR “probiotic supplementation” AND (“Bifidobacteria” AND/OR “Lactobacillus”) or “probiotics“ AND “preterm risk” OR “maternal supplementation” AND “bacterial diversity” OR “probiotics” AND “pregnancy” AND ”allergies” OR “probiotics” AND “pregnancy” AND “group B Streptococcus” OR “probiotics” AND “pregnancy” AND (“ bacteria AND/OR “bacterial diversity”) OR “probiotics” AND “pregnancy” AND “ obesity” .

142 publications were reviewed, 15 clinical trials were finally included considering above mentioned criteria (a-e).

In Table 1. we present the results of our literature research stratified to study population, probiotic strain used, intervention period, outcomes measured and study results. The studies report on several maternal outcomes including gestational diabetes (GDM), inflammatory markers and characteristics of the vaginal, gut or breast milk microbiome. Halkjaer et al. [30] supplemented 50 obese pregnant women with *Bifidobacteria spp.* and *Lactobacillus spp.* No significant changes in frequency of GDM (gestational diabetes mellitus), maternal HbA_1_C or infant birth weight were found. However, the gastrointestinal microbiome of supplemented pregnant women was characterized by an increased α- diversity when compared to untreated controls. Unlike these results, Luoto et al. [31] reported a reduced risk of GDM (OR = 0.27 (95% CI 0.11, 0.62); *P* = 0.002) after probiotic supplementation (*Bifidobacteria spp.* and *Lactobacillus spp.)* of 256 women throughout all trimesters of pregnancy. Study results of probiotic effects on inflammatory markers during pregnancy and perinatal period are inconclusive. Vitali et al. [32] reported on significant decreases of serum anti-inflammatory cytokines such as IL-10 (interleukin) and IL-4 in 30 women. In mothers-to-be with GDM, decreased levels of C-reactive protein were found after supplementation of *Bifidobacteria spp.* and *Lactobacillus spp.* [33] However, Dewanto et al. [34] could not reveal changes of IL-8 in breast milk, nor in fecal α-1-antitrypsin or calprotectin levels in neonatal stool.

Several studies examined probiotic effects in microbiome characteristics of different niches (rectovaginal, gastrointestinal, breast milk) with heterogenous results. Abundances of *Bifidobacteria spp.* and *Lactobacillus spp.* were significantly increased in colostrum and mature milk [35], but changes in diversity of maternal vaginal microbiome’s composition have not been observed [36]. Further studies showed that the abundances of group B Streptococcus and several *Candida spp.* in the vaginal microbiome were diminished after probiotic supplementation of pregnant women [37, 38]. To our best knowledge, there is only one study that reports on HMO composition in breast milk after probiotic supplementation during pregnancy [1]. Various HMOs showed a significant increase in human milk following the intervention, which was most pronounced for 3-fucosyllactose (p = 0.008) and 3’-sialyllactose (*p* = 0.006). The authors hypothesized a shift from 6’ sialylation to 3’ sialylation. These changes might be associated with increased abundance in mammary gland after probiotic supplementation through the entero-mammary-pathway (see Fig. 1). Furthermore, various studies aimed at clinical outcomes of infants whose mother’s received probiotics during pregnancy and report on microbiome alternations. However, no significant changes were seen in children’s microbiome composition and in α- and β-diversity [39]. Notably, a decreased risk for developing atopic dermatitis in the first 18 months [40] and reduced rates of positive skin prick test results were found after probiotic supplementation during pregnancy [41].

**Table 1 Tab1:** Results of literature research

Study	Study population	Type	Intervention/probiotic	Control	Intervention period	Outcomes measured	Results
Gestational diabetes (GDM)							
Halkjaer et al. [30] Denmark	50 obese pregnant women	RCT	Visbiome® 450 billion CFU Lactobacillus paracasei, plantarum, acidophilus, delbruecki; B. lactis, breve Streptococcus thermophilus	placebo	14–20 weeks of gestation until delivery	GWG, GDM, maternal HbA_1_C, infant weight	no significant group differences increased α-diversity in fecal microbiota of supplemented women
Luoto et al. [31] Norway	256 pregnant women	RCT	Lactobacillus rhamnosus GG and Bifidobacterium lactis Bb12	placebo	first trimester until delivery	frequency of gestational diabetes	significantly lower frequency of GDM no significant reduction of birth weight
Inflammatory markers							
Vitali et al. [32] Italy	30 pregnant women	RCT	VSL#3 Lactobacillus acidophilus, plantarum, paracasei, delbrueckii subsp.bulgaricus Bifidobacterium longum, breve, infantis S. thermophiles	placebo	33 to 37 weeks of gestation	cytokine secretion in women’ blood	significantly lower levels of IL-4 and IL-10 in control group
Dewanto et al. [34] Indonesia	110 pregnant women	RCT	Bifidobacterium lactis animalis HNO19	placebo	third trimester until 3 months after birth	IL-8 in breast milk, urine IFABP, faecal α-1-antytripsin (AAT) and calprotectin at birth and after 3 months	no significant alterations found between probiotic group and control group
Badehnoosh et al. [33] Iran	60 women with GDM	RCT	Lactobacillus acidophilus, lactobacillus casei, bifidobacterium bifidum.	placebo	6 weeks intervention	fasting plasma glucose, c-reactive protein, plasma malondialdehyde concentration (MDA),	significantly decrease of in fasting plasma glucose, c-reactive protein and in MDA increase of total antioxidative capacity
Mastromarino et al. [35] Italy	67 healthy pregnant women	RCT	VSL#3 Lactobacillus acidophilus, plantarum, paracasei, delbrueckii subsp.bulgaricus Bifidobacterium longum, breve, infantis S. thermophiles	placebo	36 weeks of gestation until delivery	amount Lactobacilli and Bifidobacteria in colostrum and mature milk	Significant increase in abundances of probiotic strains in probiotic group regardless the mode of delivery
Dotterud et al. [39] Norway	243 pregnant women	RCT	Lactobacillus rhamnosus GG, L acidophilus La-5, and Bifidobacterium animalis subsp. Lactis Bb-12	placebo	36 weeks of gestation up to three months postnatally	bacterial classes and genera, α- and β-diversity in children´s microbiome	no alternations in microbiome composition, α- and β-diversity
Yang et al. [36] Canada	86 pregnant women with increased nugent score	RCT	Lactobacillus rhamnosus GR-1 and Lactobacillus reuteri RC-14	placebo	12 weeks intervention starting at 13 weeks of gestation	Shannon diversity index at 13, 28 and 35 weeks of gestation in vaginal microbiome	no differences between groups
Ho et al. [37] Taiwan	110 GBS positive pregnant women	RCT	Lactobacillus rhamnosus GR-1 and Lactobacillus reuteri RC-14	placebo	21.1 ± 5 days until delivery	maternal GBS colonization	Significant decrease in GBS colonization rate in probiotic group
Ang et al. [38] Malaysia	78 pregnant women with vaginal candidiasis	RCT	Lactiplantibacillus plantarum helveticus; Lacticaseibacillus rhamnosus Lacticaseibacillus paracasei, Limosilactobacillus fermentum Lactobacillus delbrueckii subsp. Lactis	placebo	eight weeks from 14–32 weeks of gestation	abundance of Candida albicans, glabrata and Lactobacillus cripatus and jensenii in vaginal microbiome	significantly decreased abundance of C. albicans and glabrata, increased abundance of L. crispatus & L. jensenii
Atopic diseases and allergies (infants)							
Allen et al. [41] UK	554 pregnant women	RCT	Lactobacillus salivarius CUL61, 6.25 × 109 CFU/day; L. paracasei CUL08; Bifidobacterium animalis ssp. Lactis CUL34, Bifidobacterium bifidum; 1.25 ×109 CFU/day/each strain for four weeks	placebo	36 weeks of gestation to six months after delivery	Positive SPTs to food allergens (cow’s milk and egg proteins) at either 6 months or two years	Significant decrease in the rate of SPT + to cow milk and eggs in probiotic group after six months; no differences after two years.
Enomoto et al. [40] Japan	130 pregnant women	RCT	Bifidobacterium breve M-16V and Bifidobacterium longum BB536	placebo	1 month prior to delivery, postnatally for 6 months	allergic symptoms at 4, 10 and 18 months of age	significantly lower risk of developing atopic dermatitis (AD) eczema during the first 18 months of life in the probiotic group
HMOs-composition in breast milk							
Seppo et al. [1] Finland	81 colostrum samples from 1223 pregnant women	RCT	Lactobacillus rhamnosus GG, LC705, Bifidobacterium breve Bb99, Propionibacterium freudenreichii subspecies shermanii JS	placebo	36 weeks of gestation until delivery	changes in composition of human milk oligosaccharides in breast milk	significantly higher concentrations of 3-fucosyllactose and 3’-sialyllactose

*Legend GWG* gestational weight gain, *GDM* gestational diabetes mellitus, *RCT* randomized controlled trial, *GBS* group B streptococcus, *SPT* skin prick test, *CFU* colony forming unit, *IL* interleukin, *MDA* malondialdehyde, *HbA*_*1*_*C* glycolyzed hemoglobin, *C* Candida, *L* Lactobacillus

#Results refer to the group with probiotic supplementation if not otherwise indicated

Figure 1. Schematic illustration of the *entero – mammary – (neonatal) gut – pathway* which is hypothesized to be stimulated by the supplementation of probiotics during pregnancy. After maternal probiotic intake an increased abundance of *Bifidobacteria spp.* and *Lactobacillus spp.* may trigger the gut – breast axis in which probiotic bacteria, antibodies, IgA and cytokines are translocated from the gut to the mammary glands secretory cells via dendritic cells (DC) through lymph / blood circulation [42]. DCs sample commensal bacteria and immune factors by penetrating the gut mucosa via self-expressed tight junctions. An increased abundance of probiotic strains in the mammary gland cells may trigger the synthesis of HMOs as a nutritional source for *Bifidobacteria spp*., whereas the distinct mechanisms are yet unknown. Consequences for the neonatal gut microbiome include an increased abundance of probiotic bacteria which exert anti-inflammatory and infection-preventive effects by strengthening the mucosal barrier and elimination of pathogens. An improved supply of breast milk with prebiotic HMOs further supports a *Bifidobacteria* – dominated gut microbiome [43]. Beneficial effects for the neonatal “gut-immune-axis” include inhibitory effects on *Campylobacter spp.)* to the intestinal mucosa. Ancillary HMO related (2’- and 3’-Fucosyllactose) stimulation of T_H_1- lymphocytes and induction of anti-inflammatory cytokines such as IL-10 or FGF-ß distributed by regulatory T-lymphocytes is expected, alongside with increased expression of dendritic cells and maturation of naïve CD4^+^ T-lymphocytes to regulatory T-lymphocytes enhanced by certain *Bifidobacteria spp.* [44]. Short chain fatty acids (SCFA) modulate the immune tolerance by decreasing the awareness of macrophages to commensal [45, 46]. The neonatal “gut-brain-axis” is influenced by neurotransmitters such as GABA produced by *Bifidobacteria spp.* and *Lactobacillus spp.* [47]. GABA is translocated from gut to brain via blood circulation and regulates the production of the neurotransmitters like serotonin, acetylcholine and dopamine. Dysfunctions in the GABAergic system may contribute to stress associated disorders or encourage memory and cognitive impairment. [47]. Sialylated HMOs (e.g. 3’- Sialyllactose) may enhance learning, memory and language function [48], while high concentrations of 2’-Fucosyllactose in breast fed infants were found to be associated with improved motoric skills at the age of 24 months [49, 50].

**Fig. 1 Fig1:**
[figure not shown]
Effects in mother and preterm infant after probiotic supplementation. *Legend* FGF-ß Fibroblast growth factor beta, GABA Gamma-aminobutyric acid, GAD Gamma decarboxylase, GLU Glutamate, HMO Human milk oligosaccharide, IL Interleukin, SCFA Short chain fatty acids, T_H_-1 T-helper lymphocyte, Treg T regulatory lymphocyte

## Study design and methodology

### Screening and study participants

From January 2024 to January 2026 all women presenting with risk for preterm birth (e.g. cervical shortening, PPROM, vaginal bleeding, preeclampsia, HELLP syndrome) are informed about the study and asked to participate after giving their written informed consent. The women will be given probiotics from the day that they are identified with a risk of imminent preterm birth and decide to participate in this study until the delivery of the infant. We will include approximately 130 women from 20 + 0 to 36 + 6 weeks of pregnancy. The study population will be randomly divided into two groups consisting of (1) women taking probiotics during pregnancy and (2) women without probiotic supplementation. This study is registered at the German Registry for clinical studies (DRKS), DRKS00033539.

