### In- and exclusion criteria

Pregnant women of any ethnic background between 20 + 0 and 36 + 6 weeks of pregnancy who are at risk for preterm birth are included. The underlying condition (e.g. PPROM, cervical shortening, bleeding, preeclampsia, HELLP syndrome) is not decisive to inclusion. Participating patients will be included after they have been informed about the study procedures, intervention, associated responsibilities and when they have given written informed consent. Women with outpatient monitoring are also applicable for participation. Since the date of birth cannot be predicted, the study concept inevitably includes full-term children – mother pairs to be included. Pregnant women under the age of 18 years and women, who do not plan to deliver their infant at our site will be excluded primarily, because in these cases collecting the samples postpartum is not feasible. Women who decline to feed their infant with breast milk or without written consent will also be excluded.

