### Intervention/Control

Study participants are randomly assigned to receive the probiotic mixture (intervention group *n* = 73) or not (control group *n* = 73). The intervention is one capsule of Bactiol^®^ Infantis per day until delivery. The proposed number of participants is calculated based on former studies (see below). A randomization sequence was created in advance to assign mother – infant pairs to a study arm. This trial is not blinded. The women and participating doctors know whether they are in the intervention or control group, and we are not using a placebo.

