### Primary endpoint, secondary endpoints/data collection

The primary endpoint is the HMO composition (3-fucosyllactose, 3’-sialyllactose) in human breast milk after supplementation prenatally. Secondary endpoints are clinical and safety outcomes of mothers (infections, alterations in vaginal microbiome) and infants (preterm birth, sepsis, growth, gastrointestinal complications) and the effects on the microbiome composition in the rectovaginal tract of mothers at delivery and in the gut of term and preterm infants.

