### Data collection

Standardized Case Report Forms (CRFs) are used to record information from the mother prenatally and postnatally from mother and infant. At the time of inclusion (CRF inclusion), closely after birth (CRF day 3), one month after birth (CRF day 28), at three months CRF 3 m (mother + infant), one- and five-year follow- up (CRF 12 and 60 m) (see Fig. 2).

Data collected at the follow-ups will be used to measure long-term outcomes (allergies, incidence of infections, re-admissions to the hospital). The CRFs are filled in manually by the study team (neonatologist, doctoral student and study nurse). Additionally, the women will be asked to keep a diary handed out at inclusion to document regularity of probiotic intake, infections, antibiotic therapy, allergies and possible side effects during the intake of probiotics. The inclusion-CRF collects information of former participant’s medical history e.g. preexistent diseases, the course of pregnancy, former pregnancies and allergies. The follow up CRFs collect data from both, mothers and infants. CRF day 3 includes information about the delivery mode, reason for delivery, infections and risk factors for microbiome dysbiosis. In CRF day 28 information about complications in puerperium, growth parameters and feeding of the infant is collected. This data will be collected via telephone interview. In case of birth before completed 32 weeks follow-up examination will take place onsite. At follow-up information on both, mother and infant will be recorded via CRFs.

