### Statistical analysis

Subgroup analysis of previous medical history exposure to antibiotics, infections in pregnancy and indication for delivery will be performed on an exploratory basis. Adjustments for recall rate (diary, survey data) will be performed, we aim for a recall-rate of > 75%.

Statistics will be performed with R version 4.2 or higher. For graphs Graphpad prism version 10.1.2. will be used. Details of the statistical analysis will be fixed in a statistical analysis plan, which will be finalized by the trial statistician before inclusion of the last patient. The duration of probiotic intake will be taken into account in the final analysis. We will adjust our data for the different intervention timeframes using matched pair and multivariate regression analyses. However, the duration of pregnancy-accompanied probiotic therapies that were necessary to achieve the investigated outcome effects in the various studies performed (see Table 1.) have not yet been investigated. Consequently, in the case of observed effects of probiotic therapy on the HMO concentration, we will also determine the necessary duration of supplementation as a result of this study.

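### The planned subgroup by indication for delivery is formed after randomisation by unblinded decisions; use condition at entry instead, and report reason for delivery only as components of preterm birth

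*Protocol article*

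**What the plan says.** Protocol article, Screening and study participants: the trial approaches "all women presenting with risk for preterm birth (e.g. cervical shortening, PPROM, vaginal bleeding, preeclampsia, HELLP syndrome". In- and exclusion criteria adds: "The underlying condition (e.g. PPROM, cervical shortening, bleeding, preeclampsia, HELLP syndrome) is not decisive to inclusion".

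Primary endpoint, secondary endpoints/data collection: preterm birth is one undivided item among the secondary outcomes for "infants (preterm birth, sepsis, growth, gastrointestinal complications". The abstract's conclusions promise insight into the microbiome-oligosaccharide interaction and "its consequences for duration of pregnancy and outcome of infants".

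Intervention/Control: "The women and participating doctors know whether they are in the intervention or control group, and we are not using a placebo".

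Data collection: "CRF day 3 includes information about the delivery mode, reason for delivery".

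Statistical analysis: "Subgroup analysis of previous medical history exposure to antibiotics, infections in pregnancy and indication for delivery will be performed on an exploratory basis". The sentence does not name the outcome to be analysed in these subgroups. The same section leaves further detail to a statistical analysis plan, which is not shown.

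**The concern.** A subgroup analysis keeps the protection of randomisation only if the subgroup is defined by something fixed before allocation. Indication for delivery is not. It is settled at the end of pregnancy, treatment may affect it, and where delivery is a medical decision it can be made by someone who knows the arm. The women labelled as spontaneous (or indicated) deliveries in one arm need not be comparable with those given the same label in the other.

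For preterm birth the problem is sharper, because the decision to deliver fixes the indication and the gestational age together. At stake is how a difference in duration of pregnancy, a stated interest of the trial, would be explained. A subgroup result could look like a biological effect when it only reflects how deliveries were decided or labelled.

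**Working it through.** **1. The plan's own figure.** The only sizing is for milk oligosaccharides (Table 2). For 3-fucosyllactose the SD is √((164² + 232²)/2) = 200.9 and d = (413 − 312)/200.9 = 0.503. A two-sided 5% t-test with 80% power needs 63.08 per arm. Times π/3 for Mann-Whitney this is 66.06, and times 1.10 for dropout it is 72.7, so 73. The stated 73 is reproduced. It says nothing about preterm birth, for which the article gives no rate, effect or power.

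**2. When each variable is fixed.**

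| Variable | Known | Can allocation influence it? |
|---|---|---|
| Condition at entry | at enrolment | no |
| Indication or reason for delivery | at delivery (CRF day 3) | yes, through treatment or through unblinded decisions |

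**3. What conditioning on indication can do when there is no effect.** Assumptions: 100 women per arm; 50 preterm births; 20%, 40% or 60% of these indicated; all term births of spontaneous onset; no probiotic effect. In one arm, 5 women who would have delivered preterm spontaneously are delivered preterm on indication instead. With s spontaneous preterm births and 50 term births, the rate in the spontaneous subgroup is s/(s + 50) in one arm and (s − 5)/(s − 5 + 50) in the other.

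| Indicated share of preterm births | s | Arm without shift | Arm with shift | False difference in subgroup | All preterm |
|---|---|---|---|---|---|
| 20% | 40 | 40/90 = 44.4% | 35/85 = 41.2% | 3.3 points | 50 vs 50 |
| 40% | 30 | 30/80 = 37.5% | 25/75 = 33.3% | 4.2 points | 50 vs 50 |
| 60% | 20 | 20/70 = 28.6% | 15/65 = 23.1% | 5.5 points | 50 vs 50 |

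The indicated subgroup is 100% preterm in both arms by construction and shows nothing. Within strata of condition at entry the expected difference is 0, because the shift changes the route of delivery and not whether birth is preterm.

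Counted as components over all 100 women, the same shift gives −5 points for spontaneous and +5 for indicated preterm birth, with sum 0. The pair shows what happened. The spontaneous component alone would be read as a benefit of 5 points.

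**4. What no relabelling removes.** If knowing the arm changes whether indicated cases deliver preterm, the false difference in all preterm birth is f × shift, where f is the share of women with indicated delivery. For f = 0.2 to 0.5 and shifts of 10 to 20 points, it runs from 0.2 × 10 = 2 to 0.5 × 20 = 10 points. The components help to locate such a difference; they do not correct it.

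**5. Whether indicated births dilute an effect.** This can only be illustrated. Assume 73 per arm, 50% preterm birth in controls, spontaneous preterm birth halved and indicated birth unchanged. Power = Φ(|p₁ − p₂| / √([p₁(1 − p₁) + p₂(1 − p₂)]/73) − 1.96). For 0.50 vs 0.35: 0.15/0.0809 = 1.855, and Φ(−0.105) = 0.458.

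| Indicated share | All preterm | Power | Spontaneous | Power |
|---|---|---|---|---|
| 20% | 0.50 vs 0.30 | 0.71 | 0.40 vs 0.20 | 0.77 |
| 40% | 0.50 vs 0.35 | 0.46 | 0.30 vs 0.15 | 0.60 |
| 60% | 0.50 vs 0.40 | 0.23 | 0.20 vs 0.10 | 0.40 |

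The gap between the columns follows from assuming no effect on indicated births. Neither version reaches 80%.

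**The case against.** The strongest reply is proportion. Preterm birth is secondary, is not one of the three listed hypotheses and did not drive the sample size. Wide entry is deliberate and suits a trial about milk composition. Reason for delivery is already collected, the subgroup is labelled exploratory, and the detail is left to an analysis plan that is not shown. Much of this stands: an undivided preterm-birth outcome in a condensed article is no error. What remains is that the article itself names a post-randomisation variable as a subgroup factor, and the exploratory label does not make that comparison randomised.

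A reader might go further and infer that births after preeclampsia or HELLP dilute the probiotic's effect, so that conclusions should rest on spontaneous preterm birth. The documents do not support this:

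- The pathway they describe runs from maternal gut to breast to neonatal gut. Vaginal flora is a separate hypothesis about bacterial abundance and is not linked to spontaneous labour. The literature review also covers systemic maternal effects, such as gestational diabetes and inflammatory markers. That indicated births are unaffected is an outside assumption, and their share is not given.
- Indicated delivery precludes a later spontaneous birth, so the spontaneous component can show a difference where none exists (step 3).
- PPROM is an entry condition. If PPROM counted as spontaneous onset, every later preterm birth in those women would be spontaneous because of an event before randomisation, however delivery began.

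**Conclusion.** The point holds as a minor correction to one stated analysis rule. Arm comparisons within subgroups by indication for delivery are not randomised, and in an open-label trial they can be biased in either direction. The illustrated false difference of 3.3 to 5.5 points rests on an assumed 50% preterm rate, an assumed indicated share and an assumed 5-point shift. That the doctors who decide on delivery are among those who know the arm is a fair inference from "The women and participating doctors know whether they are in the intervention or control group", but the article does not spell it out. Dilution of an effect on preterm birth cannot be established from the documents, and the power figures only illustrate it. Nothing here harms the overall primary comparison.

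**What to change.** Change the Statistical analysis section, or settle it in the analysis plan before that plan is finalised:

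- Replace indication for delivery with condition at entry as the exploratory subgroup factor. Define the categories beforehand, with a rule for women who have more than one condition. The condition is known at enrolment; check that the inclusion CRF records it as a separate field.
- Keep all preterm birth, over all randomised women, as the main comparison for this secondary outcome.
- Use reason for delivery from CRF day 3 only to describe spontaneous-onset and indicated preterm birth, each with all randomised women in the denominator. Present the two side by side, and base no claim on the spontaneous component alone.
- Classify women enrolled with PPROM by how delivery began, not by the PPROM that preceded randomisation. Ideally, someone who does not know the arm makes the classification.

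The cost is wording, a classification rule and two further exploratory summaries with few events each. Women who withdraw or deliver elsewhere also need the reason for delivery. Stopping rules already intends follow-up after withdrawal, but obtaining the item from another hospital may take extra effort.
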